## 2.5. Randomization

Prior to launching recruitment, an independent statistician will randomly assign groups using a computer-generated block randomization algorithm of size 6. Groups will be assigned in a 1:1 ratio.

Two coordinators will enroll participants and collect data. REDCap will conceal each participant's allocation until directly after baseline data collection. Blinding after assignment is not possible due to the obvious nature of the intervention.

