### 2.2. Participants

**Table 2.1** describes the eligibility criteria for participation. The subject population is 60 diagnosed adult heart failure patients (confirmed by clinical exam, echocardiographic evidence, or cardiologist expert opinion), who receive primary care at one of three institutions: Columbia University Medical Center, Weill Cornell Medical Center, and New York University Langone Health.

We will recruit a purposive sample on age, sex, and race as per the institutions' adult heart failure population demographics on 1 July 2019. Potential participants will be identified by their attending cardiologist and invited to participate by the research coordinator. The attending cardiologists will not be involved in any study procedures, including data collection and randomization, and will not have access to the results except in aggregation.

| Table 2.1. Eligibility Criteria                   |                                                               |
|---------------------------------------------------|---------------------------------------------------------------|
| Inclusion Criteria                                | Exclusion Criteria                                            |
| Adult (21 years or older)                         | Healthcare professional (MD, DO, RN, etc.)                    |
| Confirmed diagnosis of heart failure              | No telephone number or email address                          |
| Able to read and speak English                    | Severe cognitive impairment or clinical diagnosis of dementia |
| Willing and able to provide informed consent      | Major psychiatric illness, including active psychosis         |
| Receives primary care from participating provider | Other illness that would preclude participation               |

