## 2.7. Procedures

**Table 2.4** describes the study procedures. In an important update as per version 2.0, participants will be now recruited by phone in addition to in-person at the outpatient clinic or inpatient unit. Recruitment by phone will be used when necessary to comply with local COVID restrictions. We will rigidly adhere to local restrictions to prevent unnecessary coronavirus infections in this vulnerable patient population.

| Table 2.4. Study Procedures |                                                                                                   |
|-----------------------------|---------------------------------------------------------------------------------------------------|
| Procedure                   | Description                                                                                       |
| Prescreening                | Patient is prescreened for eligibility and invited to participate by their cardiologist           |
| Consent                     | Participant provides verbal informed consent (by phone) or written informed consent (in-person)   |
| Baseline                    | Participant completes baseline questionnaire and health literacy screening                        |
| Allocation                  | Participant assigned to either the abbreviation group (control) or expansion group (intervention) |
| Assessment                  | Objective comprehension is assessed as per the ISO 9186 protocol                                  |

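### A single stated block size of 6 in an open trial can let the enrolling coordinators deduce up to a quarter of allocations in advance

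*Combined protocol and SAP*

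**What the plan says.** Section 2.5 sets out the allocation: "an independent statistician will randomly assign groups using a computer-generated block randomization algorithm of size 6", and "Groups will be assigned in a 1:1 ratio". It gives one block size and does not mention varying it, withholding it from site staff, or stratifying the list.

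The same section says "Two coordinators will enroll participants and collect data". On concealment it says "REDCap will conceal each participant's allocation until directly after baseline data collection", and on masking "Blinding after assignment is not possible due to the obvious nature of the intervention". Section 2.6 then has the coordinator decide whether each response is correct.

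On recruitment, section 2.2 says "We will recruit a purposive sample on age, sex, and race", and "Potential participants will be identified by their attending cardiologist and invited to participate by the research coordinator". Table 2.4 in section 2.7 gives the first step differently: "Patient is prescreened for eligibility and invited to participate by their cardiologist". The same table puts the health literacy screener after consent and immediately before allocation.

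Section 3.3 specifies an unadjusted Welch t-test on the count of terms understood, with baseline characteristics compared between arms.

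**The concern.** Concealment has two parts: the next assignment must not be visible, and it must not be predictable. REDCap secures the first. With a constant block size and open allocations, the second depends on what the coordinators know. Someone who knows that each block holds three of each arm, and has seen the earlier assignments in the block, can sometimes name the next one and can often guess it.

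This matters more here than in a masked trial. The people who enrol also learn the allocations and score the outcome, so unpredictable allocation carries much of the protection. Recruitment is not consecutive, which leaves some freedom over who is enrolled when. If patients expected to do well were enrolled, even unintentionally, when the expansion arm was due, part of the difference in scores would reflect who was enrolled. The primary test makes no adjustment that would remove it.

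**Working it through.** **Inputs.** Block size 6 and ratio 1:1 (section 2.5), so three of each arm per block. Sample size 60 (section 3.2), so 60/6 = 10 complete blocks. Planned difference 89% − 56% = 33 points (section 3.2); over the 10 terms of Table 2.3 that is 3.3 items.

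**The plan's own figure.** The protocol gives no predictability figure. Its 80% power for 60 patients can be reproduced: a two-sample t-test on a binary outcome with SD √(0.725 × 0.275) = 0.4465 gives 80.4% at 30 per arm. This does not depend on block size.

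**Upper case: block size known, one shared list, all past allocations seen.** A 3+3 block has 20 equally likely orders. An allocation is certain once one arm is used up. The best guess is the arm with more places left (a coin toss when level).

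| Position in block | Chance it is certain | Chance the best guess is right |
|---|---|---|
| 1 | 0 | 0.5 |
| 2 | 0 | 0.6 |
| 3 | 0 | 0.6 |
| 4 | 0.1 | 0.7 |
| 5 | 0.4 | 0.7 |
| 6 | 1.0 | 1.0 |
| Sum per block | 1.5 | 4.1 |

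- Certain: 1.5 × 10 = 15 of 60 (25%).
- Guessed correctly: 4.1 × 10 = 41 of 60 (68.3%), against 30 of 60 by chance.

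**Lower case: one shared list, each coordinator sees only their own half, nothing exchanged.** A forced allocation is recognised only if all three earlier patients in the used-up arm were that coordinator's own, with chance (1/2)³ = 1/8. So 15 × 1/8 = 1.9 of 60 (3%) are certain. Simulation of 4,000 trials gives the same 1.9, with 58% guessed correctly. This case still assumes that the block size and the block boundaries are known; without the size, no allocation is strictly certain.

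**Possible bias (illustration).** Assume the upper case, a score SD of 2 items, no true effect, and enrolment that raises or lowers the expected score by g items according to the guess, with no shift when the arms are level. The arms are level at position 1 always, and at positions 3 and 5 with probability 0.6 each: 1 + 0.6 + 0.6 = 2.2 per block. That leaves 6 − 2.2 = 3.8 informed guesses, of which 4.1 − 2.2/2 = 3.0 are right and 0.8 wrong. Over 10 blocks the net is 30 − 8 = 22, and the spurious difference is 22g/30 = 0.73g.

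- g = 0.5: 0.37 item, or 0.37/3.3 = 11% of the planned difference; simulated type I error about 10%.
- g = 1: 0.73 item, or 22% of it; simulated type I error about 26%.

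**Effect of varying blocks.** Simulation of 2,000 trials per scheme, with an observer who knows the set of sizes and all past allocations:

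| Scheme | Certain, of 60 | Best guess right |
|---|---|---|
| Fixed 6 | 15.0 | 68.3% |
| 4 and 6 | 3.5 | 69.0% |
| 4, 6 and 8 | 1.4 | 67.8% |

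**Precision of the sensitivity analysis.** Removing the forced allocations leaves about 60 − 15 = 45. Power for 3.3 items is then over 99% at SD 2, 95% at SD 3, and 68% at SD 4.47 (the binary-outcome SD above on a 10-item scale). These SDs are assumptions.

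**The case against.** The strongest reply is that the route to bias is narrow.

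- **Who selects.** A reader might infer that the coordinators choose the patients. The protocol does not say so: attending cardiologists identify candidates and take no part in study procedures. Under Table 2.4 they also invite, which would remove most coordinator discretion at that step; section 2.2 has the coordinator invite. This stands. What remains under either text is enrolment itself, including its timing and order.
- **Health literacy.** A reader might infer selection on health literacy specifically. The screener follows consent, so at invitation a coordinator has at most an impression. Using the score would mean delaying or dropping someone already screened, which the protocol neither describes nor forbids. It is a possibility only. The purposive targets are age, sex and race, and they also constrain choice.
- **How many.** The 25% needs knowledge of the block size and full sight of one list. The documents do not establish that the coordinators had either. This stands, and 25% is an upper figure.
- **Other safeguards.** The script, the single permitted prompt and the prior agreement on adequate answers limit scoring bias, and baseline comparisons would show a gross imbalance. They would not correct it, and they do not bear on predictability.
- **Remedy.** Varying the blocks barely changes guessing, because favouring the under-represented arm needs no knowledge of block size. This stands; the gain is in certain allocations only.
- **Timing.** Data collection was scheduled to end in August 2021 and section 2.8 reports retrospective registration, so a new list may come too late. The sensitivity analysis can still be done from the existing list.

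**Conclusion.** The weakness is real, conditional and moderate. One constant block size in an open 1:1 trial, with the same two coordinators enrolling, learning allocations and scoring, means that REDCap concealment does not prevent deduction. Depending on what the coordinators know and share, between about 3% and 25% of allocations are certain in advance and between 58% and 68% can be guessed.

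The documents do not show that selection occurred, and they do not support reading the design as one in which the coordinators foresee most allocations. Even with deliberate steering of 0.5 to 1 item in the upper case (SD 2 assumed), the spurious difference is about 0.4 to 0.7 item against a planned 3.3. The threat is to the accuracy of the estimate and to the type I error more than to the direction of an effect of the planned size.

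**What to change.** 1. For any patients not yet randomised, have the independent statistician issue a list with randomly varying block sizes (for example 4, 6 and 8). Withhold the sizes from the coordinators, from their REDCap view and from the protocol they use; the text need only say that permuted blocks of varying size are used.
2. For patients randomised under the fixed list, add a sensitivity analysis of the primary comparison that excludes those whose allocation was fully determined by earlier ones in the block. These can be identified from the list alone. It does not address allocations made at merely favourable odds.
3. State who knew the block size, whether both coordinators worked from one list and saw each other's allocations, and the point after which a participant must be randomised.
4. Reconcile section 2.2 with Table 2.4 on who invites patients.

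Cost: one new list and a few sentences. With blocks of up to 8, a last incomplete block can leave the arms at most 4 patients apart, with negligible loss of power. The sensitivity analysis uses about 45 patients and is less precise, so it should support the primary analysis and not replace it.

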## 2.6. Outcome

The primary outcome will be objective comprehension, assessed using the International Organization for Standardization Method for Testing Comprehension (ISO 9186) as previously adapted for oral administration by an objective observer. ISO 9186 is a well-known standardized protocol for assessing objective comprehension.

Briefly, the coordinator primes participants to the task (**Figure 2.2**) and reads the paragraph aloud. Then, the coordinator asks participants to verbally explain each abbreviation's or expansion's meaning as per ISO 9186. If the response is incomplete or incorrect, the coordinator can only say "tell me more," to prevent them from biasing the response.

We will consider the response correct if the participant can describe the abbreviation or expansion, as determined by the coordinator. The coordinators will discuss the potential scope and depth of adequate responses prior to recruitment to ensure standardization, and any unclear classifications will be discussed by the research team.

Next, I'm going to ask you to read a paragraph.

You may not understand every word in this paragraph and that's ok.

Our goal is to find out what you don't understand, so we can make it more understandable in the future.

[Participant reads paragraph with either abbreviations or expansions]

Now, I'm going to ask you what some of the words mean.

Even if it seems obvious, just say it.

If you don't know, it's okay to say "I don't know."

[Ask about meaning of each abbreviation or expansion]

**Figure 2.2.** Introductory script to ISO 9186 protocol. Actions depicted in [gray]

## 2.7. Procedures

**Table 2.4** describes the study procedures. In an important update as per version 2.0, participants will be now recruited by phone in addition to in-person at the outpatient clinic or inpatient unit. Recruitment by phone will be used when necessary to comply with local COVID restrictions. We will rigidly adhere to local restrictions to prevent unnecessary coronavirus infections in this vulnerable patient population.

| Table 2.4. Study Procedures |                                                                                                   |
|-----------------------------|---------------------------------------------------------------------------------------------------|
| Procedure                   | Description                                                                                       |
| Prescreening                | Patient is prescreened for eligibility and invited to participate by their cardiologist           |
| Consent                     | Participant provides verbal informed consent (by phone) or written informed consent (in-person)   |
| Baseline                    | Participant completes baseline questionnaire and health literacy screening                        |
| Allocation                  | Participant assigned to either the abbreviation group (control) or expansion group (intervention) |
| Assessment                  | Objective comprehension is assessed as per the ISO 9186 protocol                                  |

## 2.8. Adherence to Guidelines

This study will be performed in accordance with World Medical Association Declaration of Helsinki. The Weill Cornell Medicine Institutional Review Board has approved the trial and all participants will provide informed consent. We will conduct and report this trial in accordance with CONSORT.

Notably, this trial was not classified as a clinical trial under the NIH definition at the time it was funded, so it was not registered prospectively. However, the journal has asked that it be registered retrospectively as they have determined this study to meet the ICMJE definition of a clinical trial. Accordingly, the trial has been retrospectively registered with ClinicalTrials.gov (NCT05297942).

## 3. Statistical Analysis

### 3.1. Data Management

The coordinator will enter baseline data and outcome data electronically into REDCap at the time of collection. The coordinators will be trained in the ISO 9186 protocol and a pre-standardized REDCap survey will be used throughout to ensure that data collection is standardized. Data transfer between REDCap and computers for statistical analysis will be HIPAA-compliant and the data will be stored in a secure server environment.

### 3.2. Sample Size Calculation

Based on the clinician ratings, the estimated comprehension of expansions is 89% and the estimated comprehension of abbreviations is 56%. Therefore, we have anticipated a comprehension rate of 89% for the intervention and 56% for the control group. Our planned sample size of 60 patients will provide 80% power to detect this 33 percentage point difference in our primary outcome at the 5% significance level. We will stop recruitment once 60 participants have completed the trial.

### 3.3. Main Analysis

We will use a two-sided unequal variances t-test with a significance threshold of  $P < 0.05$  to analyze differences in overall comprehension (primary outcome) between study groups based on a summary (count) score of the total number of abbreviated or expanded terms comprehended by the patient. Fisher's exact test of independence with a significance threshold of  $P < 0.05$  will be used to examine differences between abbreviated and expanded versions of each individual term. Uncertainty will be estimated using standard 95% confidence intervals.

We will conduct bivariate analyses to assess whether baseline characteristics differ by group. Nominal variables will be compared using Fisher's exact tests, while ordinal and numerical variables will be compared using Wilcoxon rank-sum tests. Participants will be analyzed according to their original allocation. One goal of the study design is to avoid missing data, and we do not anticipate having missing data. However, in the event of missing data, we will use multiple imputation methods. Analyses will be performed in R Version 3.6.3.

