## 1.3. Study Objectives

The overall objective is to establish patient comprehension of abbreviations vs. expansions in clinical text, using several control mechanisms to isolate the main effect of expansion. This assessment is intended to:

- (1) characterize the extent of miscommunication due to abbreviations in health records;
- (2) evaluate the need for potential solutions such as automated abbreviation expansion.

We *hypothesized* that abbreviation expansion would improve patient comprehension of abbreviations in clinical text. As a secondary analysis, the study will determine associations between comprehension of abbreviations and common characteristics, including education level, socioeconomic status, and health literacy.

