### 2.3. Baseline Data

All baseline data will be recorded in REDCap. REDCap is a secure, HIPAA-compliant web application for building and managing online surveys and databases. REDCap is specifically geared to support online or offline data capture for research studies and operations.

**Table 2.2** describes the baseline data that will be collected. Demographic characteristics included age, gender, race, ethnicity, and preferred language, and socioeconomic characteristics included educational attainment, insurance type, financial resources, and disability status. To estimate health literacy, we use the 3-item Brief Health Literacy Screener.

**Table 2.2.** Baseline Data

| Data Field           | Question Text                                      | Coded Responses                                                                                           |
|----------------------|----------------------------------------------------|-----------------------------------------------------------------------------------------------------------|
| mrn_empi             | Please enter patient's EMPI number:                | Text (10 digit EMPI)                                                                                      |
| survey_taker         | Who is completing this survey?                     | 1 Researcher
2 Patient                                                                                 |
| location             | Where was the participant recruited?               | 1 Inpatient
2 Outpatient                                                                               |
| institution          | Where does the participant receive primary care?   | Text (prefilled institution)                                                                              |
| age                  | What is your age?                                  | Text (number, minimum 18, maximum 110)                                                                    |
| gender               | What gender do you identify as?                    | 1 Male
2 Female
3 Other                                                                             |
| gender_other         | Please specify "Other":                            | Text (required)                                                                                           |

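### For the comparison between arms, section 3.3 uses baseline data only in significance tests of randomised groups and plans no covariate-adjusted estimate, although health literacy and education are collected before allocation

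*Combined protocol and SAP*

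**What the plan says.** - **Primary comparison (section 3.3, and the synopsis to the same effect).** "We will use a two-sided unequal variances t-test with a significance threshold of" 0.05 on P, "based on a summary (count) score of the total number of abbreviated or expanded terms comprehended by the patient". Table 2.3 has ten terms, so the score runs from 0 to 10. No covariate enters.
- **Baseline comparison (section 3.3).** "We will conduct bivariate analyses to assess whether baseline characteristics differ by group", by Fisher's exact test for nominal variables and Wilcoxon rank-sum for ordinal and numerical ones. The plan attaches no consequence to the results.
- **What is collected.** Section 2.3: "To estimate health literacy, we use the 3-item Brief Health Literacy Screener". Table 2.2 records education on nine ordered levels, plus a code 10 for patients who are unsure or decline. Under section 2.5, allocation stays concealed until baseline collection is finished.
- **Expected relevance.** Section 1.3 announces a secondary analysis of "common characteristics, including education level, socioeconomic status, and health literacy" against comprehension. Section 3.4 carries it out, within the control group only.
- **Randomisation (section 2.5).** Blocks of 6 in a 1:1 ratio, with no stratification factor described.
- **Sample size (section 3.2).** "Our planned sample size of 60 patients will provide 80% power", and "we have anticipated a comprehension rate of 89% for the intervention and 56% for the control group".

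**The concern.** Two things look wrong in how baseline data serve the arm comparison.

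First, the between-arm tests. Allocation is computer-generated and baseline is recorded before it is revealed, so any difference between arms is due to chance. A P value for that null hypothesis tells the reader nothing about whether an imbalance matters, which depends on how strongly the variable predicts the score.

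Second, the variables most likely to matter are already in the database and are left out of the effect estimate. The four control mechanisms in section 1.4 cover level of care, illness, term difficulty and written context. None of them balances health literacy or education, and the randomisation is not stratified by either. The analysis is the remaining place to deal with them. At stake are the width of the confidence interval for the main result and how far a chance imbalance in 60 patients can move the estimate.

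**Working it through.** **1. The plan's own figures.** The Table 2.3 percentages sum to 558 over ten abbreviations and 891 over ten expansions, giving means of 55.8% and 89.1%. The 56% and 89% reproduce. Treated as one binary outcome per patient at 30 per arm, power is 83.4% (pooled normal approximation) or 77.3% (Fisher's exact). The stated 80% lies between them and is matched by neither.

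The planned analysis uses the count, where the difference is 33 points × 10 terms = 3.3 terms. The documents give no SD, so a range is assumed. The noncentrality is 3.3/(SD × √(2/30)), which at SD 2 is 3.3/0.516 = 6.4. Unadjusted power is over 99.9% at SD 2, 98.7% at SD 3 and 88.1% at SD 4. The largest SDs that a 0–10 score with means 8.9 and 5.6 can have are √(8.9 × 1.1) = 3.13 and √(5.6 × 4.4) = 4.96. Even there, power is about 86%.

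**2. What adjustment does to the standard error.** For k = 2 linear covariates and N = 60, the variance ratio is approximately (1 − R²) × (N − 3)/(N − k − 3) = (1 − R²) × 57/55. The SE ratio is its square root, and the equivalent unadjusted N is 60 divided by it. R² is assumed throughout. The half-widths also assume an SD of 2 terms; unadjusted, the half-width is 1.03.

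| Assumed R² | Variance ratio | SE ratio | Equivalent N | 95% half-width (terms) |
|---|---|---|---|---|
| 0 | 1.036 | 1.02 | 58 | 1.05 |
| 0.1 | 0.933 | 0.97 | 64 | 1.00 |
| 0.2 | 0.829 | 0.91 | 72 | 0.94 |
| 0.3 | 0.725 | 0.85 | 83 | 0.88 |

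**3. Chance imbalance.** With 30 per arm, the difference in a standardised covariate has SE √(2/30) = 0.258. At R² = 0.2 and SD 2, one such SE moves the unadjusted estimate by 0.258 × √0.2 × 2 = 0.23 terms, and 1.96 of them move it by 0.45 terms.

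**4. Which robust standard error.** With arm as the only regressor, the HC2 variance is s₁²/n₁ + s₂²/n₂, the same as Welch. HC3 divides by n − 1 instead of n, so its SE is already √(30/29) = 1.017 times larger. HC2 is therefore the natural counterpart of the planned test.

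A simulation checks this on the bounded score. It used 30 per arm and Table 2.3 item rates held within 2–98%, with an assumed patient effect of SD 0.8 logits and two assumed normal covariates. The table gives the change in mean 95% interval width against Welch.

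| Mean in-sample R², control / expansion | HC2 | HC3 |
|---|---|---|
| 0.07 / 0.07 (covariates have no effect) | 1% wider | 5% wider |
| about 0.14 / 0.11 | 2% narrower | 1% wider |
| about 0.31 / 0.23 | 11% narrower | 7% narrower |

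Two useless covariates already give an in-sample R² near 0.07 with 30 patients, so these R² values overstate true prognostic strength. R² is lower in the expansion arm, where scores sit near the top of the scale.

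**5. The baseline tests.** Section 2.3 names ten characteristics, and Table 2.2 has about fifteen items that could be tested. With independent 5% tests, the chance of at least one significant difference is 1 − 0.95¹⁰ = 40% to 1 − 0.95¹⁵ = 54%. Correlated items and discrete Fisher tests would be expected to lower this.

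**The case against.** The strongest defence is that nothing planned is invalid. The Welch test is correct under randomisation, its interval already allows for chance imbalance, and power for 3.3 terms is ample without covariates. All of that stands.

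A reader might infer several stronger things that the documents do not support:

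- **That baseline data serve only the between-arm tests.** They do not. Section 3.4 uses them as predictors of comprehension in the control group. That analysis does not inform the arm difference, so the point is confined to the arm comparison.
- **That the plan expects these variables to predict the score.** Section 1.3 only says associations will be examined. It gives no correlation, so the gain could be nil or slightly negative.
- **That the gain is 60/(1 − R²), or 67, 75 and 86 patients.** That formula omits the degrees-of-freedom cost and the ceiling. Seven of the ten expansions are rated at 100%.
- **That the baseline tests will lead to post-hoc adjustment.** Section 3.3 fixes the primary test and makes nothing conditional on them. A false flag changes no planned analysis.

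Timing is a further objection. Section 2.8 reports retrospective registration, and the synopsis ends data collection in August 2021. If results by arm have been seen, a new primary model would not be pre-specified. The documents do not settle this, so the fix has to be conditional.

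**Conclusion.** The point holds for the arm comparison. Section 3.3 tests randomised groups for baseline differences, which serves no purpose, and plans no adjusted estimate although two plausible covariates are recorded before allocation. No conclusion about the planned 3.3-term difference is put at risk.

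The benefit is precision and protection from chance imbalance. The SE changes from about 2% larger at R² = 0 to about 15% smaller at R² = 0.3, and the gain is less if the expansion arm is near its ceiling. These sizes rest on assumed R² values and, for the half-widths, on an assumed SD of 2. The simulation adds its own assumptions about patient variation.

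Removing the baseline tests and recoding education code 10 are justified whatever the R². Used as coded, code 10 would rank patients who are unsure or decline above those with a doctoral degree in a Wilcoxon test or a regression. The plan states no recode. This is a worthwhile improvement to a valid analysis, not a correction of an invalid one.

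**What to change.** 1. Pre-specify a linear regression of the 0–10 score on arm, health-literacy sum score and education, with HC2 standard errors, reported beside the unadjusted Welch test. The three screener items are all coded 1 to 5 with higher meaning more difficulty, so the sum runs from 3 to 15 without reversal. Education enters as one ordered score, codes 1 to 9. If that linear form is wrong, some precision is lost, but the arm comparison stays sound under randomisation.
2. If outcomes by arm have already been seen, keep Welch as primary and label the adjusted model a sensitivity analysis.
3. Treat education code 10 as unknown, and state how unknown values are handled. The multiple imputation already named in section 3.3 would serve.
4. Replace the between-arm baseline tests with a descriptive table by arm, without P values.

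The cost is two degrees of freedom, an interval about 1–2% wider if the covariates are not prognostic, and the handling of any unknown education values. No new data are needed.
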